## Abstract

**Background:**

Osteoarthritis (OA) is a health condition sensitive to patient’s preferences and values regarding the benefits and risks of the different treatment options. In this sense, patient decision aids (PtDA) can play an important role in helping patients to incorporate their values, needs, and preferences into the decision-making process, thus improving person-centered care. Previous research has focused almost exclusively on knee OA, and therefore, the aim of this study is to develop and evaluate the effectiveness of a PtDA for patients with hip OA.

**Methods:**

The general design consists of two phases: (1) design a web-based PtDA for patients with hip OA, following the recommended procedures: systematic review of safety/effectiveness of treatments, and an iterative process of development with the help of an Advisory Committee composed of health professionals and patients, and (2) to evaluate the impact of the PtDA on hip OA patients’ decision-making process related with their treatment. For that aim, a multicenter randomized controlled trial will be carried out with 124 patients with hip OA in Tenerife (Spain) comparing intervention or usual care.

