#### Randomization and allocation concealment

Computer-based randomization with Stata® 15.0 will be performed centrally by an independent researcher (allocation rate 1:1). Randomization will be stratified by patient inclusion in waiting list for arthroplasty (yes/no). Sealed envelopes with each patient’ allocation will be prepared, which will be opened only after the patient sign the informed consent for participation in the study. The nature of the intervention makes impossible to blind patients and researchers to group allocation.

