#### Sample size calculation

Assuming type I and II errors of 0.05 and 0.20 respectively, a total of 126 patients (63 per group) are needed in order to detect a medium effect size (Cohen’s *d* = 0.5) [26] in the primary dependent variable (DCS). No losses are expected given that the post-intervention assessment will take place immediately after the application of the PtDA.

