#### Statistical analysis

Data will be analyzed on an intention-to-treat basis, although given the nature of the intervention, we do not expect relevant protocol deviations. The baseline equivalence of the randomized groups will be assessed by means of Student’s *t* test and *χ*^2^ test, for continuous and categorical variables, respectively. To analyze the effect of the intervention on the primary outcome (DCS), mixed linear regression model with intervention as independent variable will be used, adjusting for DCS baseline scores and sociodemographic or clinical variables which show significant between-group differences at baseline. Center will be included as a random intercept to control for the potential intraclass correlation. The same analysis will be carried out for the remaining continuous outcomes. Treatment preference will be analyzed by means of *χ*^2^ test. Concordance between values and intention to undergo arthroplasty will be calculated by means of a method similar to the one proposed by Sepucha et al. [27]: first, a binary variable will be created, with a value of 1 for participants who prefer arthroplasty and scored 4 or 5 in intention to undergo it, and zero for the remaining patients. Second, a mixed logistic regression model will be performed with patients’ values as independent variables and intention to undergo arthroplasty (vs. other treatments) as dependent variable. Significant predictors will be retained in the model and the predicted score for each patient will be calculated. Patients with a predicted score equal or higher (lower) than 0.5 and intention to (not) undergo arthroplasty will be classified as concordant, and the remaining ones as not concordant. Finally, the effect of the DA in the number of concordant patients, as well as the number who make a quality decision, will be assessed with mixed logistic regression. For all outcomes, we will explore the interaction of the intervention with sex and education. Analyses will be performed with Stata® 15.0.

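### The abstract plans 124 patients, but the sample size section requires 126 (63 per group), and only 126 follows from the stated inputs

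*Protocol article*

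**What the plan says.** The Methods paragraph of the abstract announces that "a multicenter randomized controlled trial will be carried out with 124 patients with hip OA in Tenerife (Spain"). The section Sample size calculation, under Phase 2, derives a different total. It opens with "Assuming type I and II errors of 0.05 and 0.20 respectively" and concludes that "a total of 126 patients (63 per group) are needed in order to detect a medium effect size", namely Cohen's d of 0.5, "in the primary dependent variable (DCS"). It makes no allowance for attrition: "No losses are expected given that the post-intervention assessment will take place immediately after the application of the PtDA".

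Allocation is equal, since randomization is "performed centrally by an independent researcher (allocation rate 1:1"). The abstract's 124 would therefore mean 62 per group. The section Statistical analysis specifies a mixed linear model for the primary outcome, "adjusting for DCS baseline scores and sociodemographic or clinical variables which show significant between-group differences at baseline", with center as a random intercept. The sample size section does not mention this adjustment.

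**The concern.** The planned total is the number against which completion of recruitment, and any later shortfall, is judged. Here it has two values. A trial that closed at 124 would be complete by the abstract and two patients short by the sample size section.

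The usual explanations for two totals do not apply. An attrition allowance would make the number enrolled larger than the number needed, but here the announced number is the smaller one, and the article expects no losses. No amendment log is shown that would mark 124 as superseded. Both sentences are intact, and the 63 per group confirms the 126. According to the section Trial status, recruitment had begun in February 2020 and was due to end by October 2020, while this version is dated August 2020. The target was therefore in use when the text was written.

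**Working it through.** **Inputs.** From Sample size calculation: type I error 0.05, type II error 0.20 (power 80%), standardized difference d = 0.5, no losses. From Randomization and allocation concealment: ratio 1:1. Sidedness is not given, so both options are tried.

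**Step 1: reproduce the plan's figure.** For two means under the normal approximation, n per group = 2 × ((z for alpha + z for power) / d)².

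- Two-sided: 2 × ((1.96 + 0.8416) / 0.5)² = 62.79, rounded up to 63 per group, 126 in total. This matches the sample size section exactly.
- One-sided: 2 × ((1.645 + 0.8416) / 0.5)² = 49.5, rounded up to 50 per group, 100 in total. This matches neither figure.

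The calculation is therefore two-sided by inference.

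**Step 2: can 124 be reached from the same inputs?** The two-sided normal approximation gives 63 per group. The noncentral t calculation gives 64 per group (128 in total). Neither gives 62.

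**Step 3: what the two-patient difference is worth.** Under the normal approximation, unadjusted power = Φ(d × √(n/2) − 1.96).

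- n = 62: Φ(0.5 × √31 − 1.96) = Φ(0.824) = 79.5%
- n = 63: Φ(0.5 × √31.5 − 1.96) = Φ(0.846) = 80.1%

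| Per group | Total | Power, normal | Power, t test |
|---|---|---|---|
| 62 | 124 | 79.5% | 78.9% |
| 63 | 126 | 80.1% | 79.5% |
| 64 | 128 | 80.7% | 80.1% |

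The loss from 126 to 124 is about 0.6 percentage points by either method. The d detectable with 80% power, (1.96 + 0.8416) × √(2/n), moves from 0.499 at 63 per group to 0.503 at 62.

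**Step 4: the planned analysis.** Adjusting for baseline DCS multiplies the residual SD by √(1 − r²), where r is the correlation between baseline and post-intervention DCS. The article gives no r, so the following values are assumptions. Center effects are ignored.

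| Assumed r | Power at 124, normal | Power at 124, t test |
|---|---|---|
| 0.2 | 81.1% | 80.5% |
| 0.3 | 83.1% | 82.5% |
| 0.5 | 89.5% | 89.0% |

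By t test, 124 patients reach 80% once r is about 0.17.

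**The case against.** A reader might infer that a trial stopping at 124 would be underpowered, because 62 per group falls below 80% by both methods. That inference does not hold up, for three reasons.

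- By the method that reproduces the protocol's own figure, the gap is 79.5% against 80.1%. With d = 0.5 taken as a conventional medium effect, no decision turns on a difference of that size.
- The same strict standard would fail 126, which gives 79.5% by t test.
- These figures are for an unadjusted comparison, whereas the planned model adjusts for baseline DCS. A modest baseline correlation would put 124 above 80%, though the article neither states a correlation nor counts on one.

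It can also be said that the target is not truly ambiguous. The sample size section is the only place where a number is derived, it is consistent with itself (2 × 63 = 126), and most readers would treat 124 as an editorial slip. That is probably right, and it bears on how serious the point is. It does not make the abstract correct: the slip concerns a core design figure, in the part of the article that is read most.

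Finally, the choice between the normal approximation and the t distribution is no fault here. The stated total follows from a standard formula, and an article may leave the name of the method to the full protocol.

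**Conclusion.** The point holds as a minor internal inconsistency in the planned sample size. The abstract's 124 contradicts the 126 in the sample size section, and only 126 follows from the stated inputs. The difference is two patients, or about 0.6 percentage points of unadjusted power. The conclusion rests on a two-sided test and the normal approximation. Both are inferred from the exact match at 63 per group; neither is stated.

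The documents do not support calling the trial underpowered. Randomization, the primary analysis and the validity of the comparison are unaffected.

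**What to change.** Change 124 to 126 in the Methods paragraph of the abstract, so that it agrees with the 63 per group in the sample size section and one recruitment target stands throughout. The cost is a one-number text correction. It needs no change to the design or analysis, and no patients beyond the 126 that the sample size section already requires.

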**Discussion:**

PtDAs have been recommended as a useful and effective resource for improving PCC in many health conditions. The intervention is intended to empower patients by fostering their active participation during the decision-making process about their treatment and by ensuring they make informed decisions congruent with their values and preferences. This study will contribute to the scientific knowledge about effectiveness of PtDAs in hip OA, in order to improve the quality of health care offered to these patients.

**Trial registration:**

ClinicalTrials.gov NCT04241978. Registered on 24 January 2020.

## Background

Osteoarthritis (OA) is one of the most prevalent chronic diseases [1], which affects more than 70% of people older than 50 years, and its prevalence clearly increases with age until 70 years old [2]. It can affect any joint, but preferably affects the knee, hands, hip, and spine [3]. Pain, stiffness, and loss of functionality caused by OA have an important impact in the quality of life of patients [4, 5]. Furthermore, OA represents a high economic burden for society, due to its direct and indirect health costs [6]. As a chronic disease, OA is associated with long-term multicomorbidity and polymedication.

Conservative therapeutic options for hip OA include exercise, weight loss, and walking aids, as well as drugs and corticosteroids injections in more advanced stages. When these options fail to improve symptoms, a surgical intervention called arthroplasty or joint replacement is recommended, with some variations depending on the damaged joint. This technique has been shown to be safe and effective [7], although like any other surgical procedure, it implies risks such as infection, thromboembolism, or the need for re-intervention due to problems in the prosthesis [8]. Indication for arthroplasty is not straightforward, since subjective symptoms are not highly correlated with the cartilage deterioration observed in radiographic images [9]. This fact, along with the existing uncertainty about the absolute and relative efficacy of conservative treatments, makes OA a preference-sensitive condition, in which patients’ values and preferences regarding the benefits and risks associated with different treatment options should play a decisive role when making treatment decisions [10]. A shared decision-making (SDM) process thus seems a necessary approach in this health condition, providing patients with reliable information and promoting their involvement in decision-making, according to the principles of the patient-centered care model [11].

Patient decision aids (PtDAs) are one of the most used interventions to promote SDM and help patients to decide between different treatments options [12]. They provide information on a specific health problem and its available treatments, including quantitative information about their risks and benefits, and other characteristics relevant for making a decision. They also addresses patient’s values and preferences regarding those characteristics and potential consequences, implicitly or explicitly promoting reflection about those own values/preferences. PtDAs have shown to improve patients’ knowledge about the disease and treatments, their decisional conflict, the concordance between patients’ preferences and their actual choices, or their involvement in decision-making, among other variables [13]. In the field of OA, the few existing studies have been focused on knee OA [14] or included hip patients but did not report separate analyses for them [15, 16]. Because hip OA has its own characteristics and given the existing shortages in this field, the aim of this study is to develop a PtDAs for hip OA and evaluate its effectiveness on the improvement of patients’ decisional process.

## Methods/design

This clinical trial protocol follows the Standard Protocol Items: Recommendations for Interventional Trials (SPIRIT) 2013 statement [17] (see Additional file 1). Flow of participants are presented in Fig. 1 and the schedule of enrollment, intervention, and assessments is shown in Fig. 2. Any future protocol modification will be registered in the ClinicalTrials.gov database and communicated to the Scientific and Ethics Committee of the University Hospital Nuestra Señora de la Candelaria (Tenerife, Spain).

**Fig. 1 Fig1:**
[figure not shown]
Flow of participants

**Fig. 2 Fig2:**
[figure not shown]
Schedule of enrolment, interventions, and assessments (SPIRIT checklist)

### Study design

The general design of the study consists of two phases: (1) development of a web-based PtDA for hip OA patients and (2) assessment of its effectiveness in a randomized controlled trial (RCT).

### Phase 1: Development of a web-based PtDA

The procedure for the development of the PtDA will consist of the following steps:
We performed two systematic reviews to identify evidence on hip OA treatments’ effectiveness (search strategy: “hip osteoarthritis AND treatment” in the title), on one side, and decision support interventions for hip and knee OA patients, on the other. We consulted the databases Medline, Embase, and WOS on January 2019. For OA treatments, we only included clinical practice guidelines and systematic reviews with meta-analysis, prioritizing those more recent with enough quality. For the second review, we included all type of empirical studies which applied a PtDA for hip and knee OA patients, with the only aim of identifying the PtDAs and try to access to its content.The Project Management Group will be composed of a *scientific team* (researchers and clinical experts) with expertise in assessing the quality of the evidence presented to the Advisory Committee, and in its interpretation, and a *technical team* (web developers and designers). An Advisory Committee will also be created with 6–8 external primary and specialized care professionals (i.e., traumatology, rheumatology, physiotherapy, rehabilitation) with experience in hip OA management, and/or patient decision-making, and 3–4 individuals living with hip OA and their families and/or caregivers.Evidence synthesis and prototype of the PtDA: the scientific team will analyze and discuss the evidence on the efficacy and safety of the different treatment options, based on the results of the systematic review, and a first draft of the PtDA contents and structure will be developed following the International Patients Decision Aid Standards (IPDAS) [12]. Along with the technical team, format and presentation issues will be discussed. At the end of this phase, a first version of the PtDA will be prepared.Review and evaluation of contents: the PtDA will be sent to all members of the Advisory Committee. Content and presentation issues will be reviewed and refined, in an iterative process that will result in a second version of the PtDA. The review will be through virtual or face-to-face meetings, according to the availability of the members of Advisory Committee. There is not a predefined number of review cycles, and it will depend on the time schedule of the project and the consensus reached in the successive reviews.Field testing: this new version of the PtDA will be tested in individual interviews with 10 hip OA patients (with and without previous arthroplasty), who will evaluate its acceptability in terms of content (quantity, clarity and usefulness of information), structure, format, and navigability. Qualitative and quantitative information will be collected. After modifying those aspects highlighted by patients in order to improve the PtDA, it will be ready to evaluate its effectiveness.

### Phase 2: Assessment of effectiveness

#### Study design and setting

A parallel, multicenter, superiority RCT will be carried out in hospitals and primary and specialty care centers of Tenerife (Spain). Patients will be randomly allocated to intervention (web-based PtDA) or control group (general information about OA).

#### Eligibility criteria

Adult patients with a diagnosis of hip OA, eligible for either surgical or non-surgical management, and with fluency to read, write, and speak Spanish will be included in the trial. Exclusion criteria will be as follows: previous hip arthroplasty, patients with terminal illnesses, be participating in other trials, or mental or sensory alterations that impede or hinder the response to the measurement instruments or do not have the capacity to make decisions.

#### Randomization and allocation concealment

Computer-based randomization with Stata® 15.0 will be performed centrally by an independent researcher (allocation rate 1:1). Randomization will be stratified by patient inclusion in waiting list for arthroplasty (yes/no). Sealed envelopes with each patient’ allocation will be prepared, which will be opened only after the patient sign the informed consent for participation in the study. The nature of the intervention makes impossible to blind patients and researchers to group allocation.

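### Randomisation is stratified by waiting-list status, but no outcome model includes that factor and the covariate rule will almost never admit it; the cost is zero to modest and conservative, and one prespecified term removes it

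*Protocol article*

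**What the plan says.** Under Randomization and allocation concealment, the article gives a central 1:1 computer allocation with a single stratification factor: "Randomization will be stratified by patient inclusion in waiting list for arthroplasty (yes/no". Block size, or whether blocks are used, is not stated.

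Under Outcome measures, waiting-list status is listed with the clinical control variables collected in the baseline telephone call, so it is known for every patient.

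Under Statistical analysis, the primary analysis is a "mixed linear regression model with intervention as independent variable will be used, adjusting for DCS baseline scores". Center is a random intercept. Any other demographic or clinical characteristic is added only when its baseline comparison between arms reaches significance. The remaining continuous outcomes use the same model. Concordance and decision quality are compared between arms by mixed logistic regression. Waiting-list status is named in none of these models.

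**The concern.** An analysis should normally carry the factor by which the trial randomises. Stratification takes the factor's contribution out of the difference between arms. If the factor is left out of the model, its contribution stays in the residual variance. The reported standard error can then exceed the true sampling variability of the estimate, giving a confidence interval that is too wide and a test that runs below its nominal level.

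The covariate rule makes the omission close to permanent. It selects on imbalance, and stratification exists to prevent imbalance in this factor. The variable that the design singles out is therefore among the least likely to be adjusted for.

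The factor may well be prognostic. The primary outcome is conflict about treatment choice, and several secondary outcomes concern arthroplasty directly. Being listed for that operation plausibly bears on all of them.

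**Working it through.** **1. The plan's own figure.** Inputs from Sample size calculation: "Assuming type I and II errors of 0.05 and 0.20 respectively", d = 0.5, and "a total of 126 patients (63 per group) are needed". With a two-sided test, n per arm = 2(1.960 + 0.842)² / 0.5² = 62.8, so 63 per arm and 126 in total. This matches. Power at 63 per arm is Φ(0.5 × √(63/2) − 1.960) = Φ(2.806 − 1.960) = 80.1% (79.5% by the t distribution). The calculation takes no credit for covariates.

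**2. Can the covariate rule admit the factor?** Let m of the 126 patients be on the waiting list. Let the arms differ by D patients in each stratum, in opposite directions, with 63 per arm. The chi-square statistic is then 126 × D² / [m(126 − m)]. Permuted blocks of size B limit D to B/2 at most.

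- Blocks of 8, m = 20: 126 × 16 / (20 × 106) = 0.95, p = 0.33.
- Blocks of 4, m = 63: 126 × 4 / (63 × 63) = 0.13, p = 0.72.

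Across blocks of 4 to 8 and m = 20, 38 or 63, these bounding cases give p between 0.33 and 0.72, so the factor cannot reach significance. In simulations of 126 patients (blocks of 4 or 8, 4,000 runs per scenario) it was selected in 0 runs. With unblocked allocation inside strata it was selected in about 5% of runs. Block sizes and the proportion on the list are assumptions.

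**3. Cost in the linear model.** Let R² be the share of residual DCS variance, after baseline DCS, that waiting-list status explains. No value is given, so a range is used, with d = 0.5 on the residual SD.

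- Standard error without the term relative to with it: 1/√(1 − R²).
- Power with the term: Φ(2.806/√(1 − R²) − 1.960).
- Power without the term, blocked lists: Φ((2.806 − 1.960)/√(1 − R²)), because the estimate varies less than its standard error says.
- Type I error without the term, blocked lists: 2[1 − Φ(1.960/√(1 − R²))].

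| R² | SE ratio | Power with term | Power without, blocked | Type I error without, blocked |
|---|---|---|---|---|
| 0% | 1.00 | 80.1% | 80.1% | 5.0% |
| 2% | 1.01 | 80.9% | 80.4% | 4.8% |
| 5% | 1.03 | 82.1% | 80.7% | 4.4% |
| 10% | 1.05 | 84.1% | 81.4% | 3.9% |
| 20% | 1.12 | 88.1% | 82.8% | 2.8% |

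The gain over the 80.1% of the sample size calculation is thus 0, 0.8, 2.0, 4.0 or 8.0 points. Against the planned model under blocking it is smaller: 0, 0.5, 1.4, 2.7 or 5.3 points.

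**4. Simulation check.** With blocked lists, the mean standard error without the stratum was 1.01, 1.03, 1.05 and 1.12 times that with it at R² = 2, 5, 10 and 20%. The power difference was about 0.5, 1.5, 2.7 and 6 points. Type I error without the stratum was 4.5–5.3, 4.0–4.3, 3.4–4.2 and 2.6–3.1% (Monte Carlo error about 0.3 points). At R² = 0 there was no difference. With unblocked lists, type I error without the stratum was 4.5–5.1%, so there the standard error is right and only precision is forgone.

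Center was not simulated, and nothing was computed for the logistic models.

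**The case against.** The strongest reply is that nothing here endangers the trial's conclusion. That stands. In the linear model the effect estimate is unbiased and the error is at worst conservative. A reader might infer that the trial is underpowered. The documents do not support that: the sample size takes no credit for covariates, and at d = 0.5 the planned model keeps its design power. Power is lost only relative to a better model.

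Second, the size is unknown. That also stands. The range includes zero, and a standard error overstated by more than about 10% needs the factor to explain nearly a fifth of the residual variance, which nothing in the article shows. Baseline DCS is already in the model and may carry much of what waiting-list status would add. The center intercept may absorb more if listed patients cluster in certain centers, though the article does not say whether they do.

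Third, a reader might infer that the confidence interval and p-value are certain to mismatch the randomisation. That needs blocked lists, which are likely but not stated.

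Fourth, a reader might want a waiting-list interaction because the plan says "For all outcomes, we will explore the interaction of the intervention with sex and education". Those interactions are exploratory, and stratifying for balance does not oblige a subgroup test. Leaving it out is not a defect.

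Finally, covariate choice could be left to a statistical analysis plan. Here the article is not silent: it fixes an entry rule, and a plan that follows the rule inherits the problem.

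**Conclusion.** The point holds as a recommended improvement to the analysis, not as a threat to validity. The only stratification factor is in no outcome model, and the stated rule would admit it essentially never with blocked lists and about 5% of the time without.

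The consequence is conditional. If waiting-list status predicts the outcome beyond baseline DCS and center, precision is forgone; if lists are also blocked, the standard error is too large and the test conservative. For an assumed residual R² of 2–10% the standard error is 1–5% larger than necessary and power at d = 0.5 is about 0.5 to 4 points lower than it could be, depending on blocking. At 20% the figures are 12% and about 5 to 8 points. At zero there is no cost.

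These sizes apply to the linear models only. In the logistic models, omitting a prognostic stratum also tends to draw the odds ratio towards 1, but that was not quantified.

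**What to change.** State in Statistical analysis that waiting-list status (yes/no) is a prespecified fixed covariate, whatever the baseline tests show, in:

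- the DCS model;
- the mixed linear models for the other continuous outcomes;
- the mixed logistic models that compare the arms on concordance and on decision quality.

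The separate logistic model that relates patients' values to intention, used to derive concordance, does not compare the arms and is not part of this change.

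The cost is one degree of freedom per model and a change of wording. The variable is already collected, and the sample size stays at 126. The change is most credible if recorded before outcome data are analysed.
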